## Abstract

**Background:**

Packed red blood cell (PRBC) transfusion is required in hematology patients treated with chemotherapy for acute leukemia, autologous (auto) or allogeneic (allo) hematopoietic stem cell transplantation (HSCT). In certain situations like septic shock, hip surgery, coronary disease or gastrointestinal hemorrhage, a restrictive transfusion strategy is associated with a reduction of infection and death. A transfusion strategy using a single PRBC unit has been retrospectively investigated and showed a safe reduction of PRBC consumption and costs. We therefore designed a study to prospectively demonstrate that the transfusion of a single PRBC unit is safe and not inferior to standard care.

**Methods:**

The 1versus2 trial is a randomized trial which will determine if a single-unit transfusion policy is not inferior to a double-unit transfusion policy. The primary endpoint is the incidence of severe complication (grade ≥ 3) defined as stroke, transient ischemic attack, acute coronary syndrome, heart failure, elevated troponin level, intensive care unit transfer, death, new pulmonary infiltrates, and transfusion-related infections during hospital stays. The secondary endpoint is the number of PRBC units transfused per patient per hospital stay. Two hundred and thirty patients will be randomized to receive a single unit or double unit every time the hemoglobin level is less than 8 g/dL. All patients admitted for induction remission chemotherapy, auto-HSCT or allo-HSCT in hematology intensive care units will be eligible for inclusion. Sample size calculation has determined that a patient population of 230 will be required to prove that the 1-unit PRBC strategy is non-inferior to the 2-unit PRBC strategy. Hemoglobin threshold for transfusion is below 8 g/dL. Estimated percentage of complication-free hospital stays is 93 %. In a non-inferiority hypothesis, the number of patients to include is 230 with a power of 90 % and an alpha risk of 5 %.

**Trial Registration:**

14**–**128; Clinicaltrials.gov NCT02461264 (registered on 3 June 2015)

We also need a trial with high-level evidence to reduce the number of transfusions and the cost of hospitalization. If the single-unit policy proves to be non-inferior compared to the standard of care, it would change decennials’ years of practice for a large number of patients. If it reduces the cost of hospitalization, the economic impact would be very important for the wider society.

## Objective

The aim of the study is to demonstrate, in a prospective non-inferiority randomized study in a selective population of patients receiving chemotherapy in an intensive hematological unit, that a strategy using a single-unit transfusion is non-inferior to a two-unit transfusion in terms of severe complications and also leads to a cost reduction.

## Methods/Design

### Design

This is a prospective, multicenter, two-arm randomized study. The study will be held in an intensive care hematological ward of three hospitals (Amiens, Caen and Rouen). The transfusion of a single PRBC unit (1PRBC arm – arm B) per day in case of symptomatic anemia or hemoglobin level below 8 g/dL will be compared to the standard strategy of using a transfusion of 2 PRBC units at once (2PRBC arm – arm A).

### Study population

Eligible patients are adults (≥ 18 years) hospitalized in an intensive hematological ward for remission-induction chemotherapy, auto-HSCT or allo-HSCT with a predictable need for PRBC transfusion.

Exclusion criteria are the following: acute promyelocytic leukemia, known ischemic heart disease, acute or chronic respiratory disease, history of ischemic stroke, disseminated intravascular coagulation, hemorrhagic syndrome, HSCT conditioning not usually associated with PRBC transfusion need such as auto-HSCT conditioned with alkeran (myeloma patients), non-myelo-ablative allo-HSCT conditioned using only fludarabine and total body irradiation (TBI) 2 gray, erythropoietin treatment, autoimmune hemolytic anemia, pregnancy, renal impairment with an estimated (modified diet in renal disease; MDRD) creatinine clearance < 50 ml/min, chronic liver disease or day-1 (AST/ALT ) ≥ 2.5 upper limit of normal (ULN) (except in leukemic disease), total bilirubin ≥ 1.5 ULN, cirrhosis, age < 18 years, or any organ failure.

### Consent and ethical consideration

The study protocol and information forms were approved by the competent French legal authority (Comité de Protection des Personnes Nord Ouest III, registration number: 2014-A01473-44; date of approval 5 January 2015). Patients will be informed verbally and provided with a written document about the 1versus2 study by the investigators. Patients will be informed about the trial and their right to refuse participation. Informed consent will be signed by each participant.

### Randomization

Randomization codes have been generated and secured by an independent statistician from Centre Hospitalier Universitaire of Caen. The codes have been made available to a Good Manufacturing Practice (GMP) certified clinical trial supply company, which has prepared the treatment packs in accordance with the randomization list. The randomization will be stratified by center and reason for hospitalization.

### Treatment and study intervention

The study protocol and both arms of randomization are detailed in Fig. 1. Patients randomized in arm A will receive 2 PRBC units if their hemoglobin level is below 8 g/dL during hospitalization and until 1 month after discharge. Patients randomized in arm B (experimental arm) will receive a single PRBC unit if their hemoglobin is below 8 g/dL during hospitalization and until 1 month after discharge. All PRBC units are leukodepleted, and matched according to French policies. Auto-SCT patients will receive irradiated PRBC units and allo-SCT recipients cytomegalovirus (CMV) seronegative irradiated PRBC units [8].

**Fig. 1 Fig1:**
[figure not shown]
Overview of the study protocol design

### Data collection and follow-up

Details of the flowchart and patient follow-up are summarized in Table 1. Each subject who meets the inclusion criteria, verified by the clinician investigator in charge of medical care, will be offered the opportunity enter the study during a meeting in consultation or at first day of hospitalization. The investigator will retrieve the patient consent form at day zero. The following data will be collected at inclusion: vital signs (heart rate, arterial blood pressure, and respiratory rate), weight, and abnormal clinical signs on examination. Quality of Life in Cancer Patients-30 (QLC30), Functional Assessment of Cancer Therapy (FACT) form and EuroQol 5 dimensions (EQ-5D) data will be collected and an electrocardiogram will be performed at inclusion, the end of hospitalization stay and at 1 month after discharge. Creatinine level, blood count and troponin blood level will be collected at inclusion. During the hospitalization stay, blood count and transfusion data will be collected every day until discharge. At the end of the study (1 month follow-up), vital status, and the number of RBP transfused after leaving the hospital and the duration of hospital stay will be recorded. Each complication encountered en route to meeting the primary endpoint will also be recorded.

**Table 1 Tab1:** Flowchart of a patient follow-up

	Screening D-28 to D-1	DO inclusion	At each transfusion	End of hospitalization	One month after hospitalization
Inclusion and exclusion criteria	X				
Patient information	X				
Signed informed consent		X			
QLC30, FACT, EQ-5D questionnaires		X		X	X
Randomization		X			
Clinical assessment		X		X	X
ECG		X			
Laboratory tests – troponin		X			
Biological tests		X	daily	X	X
Transfusion parameters			X		
Complications/Adverse events					X
Alive or dead status					X

*EQ-5D* EuroQol 5 dimensions, *FACT* Functional Assessment of Cancer Therapy, *QLC30* Quality of Life in Cancer Patients-30,D-28 to D-1: day-28 to day -1

A cost-effectiveness analysis will be performed alongside the clinical evaluation. By reference to Haute Autorité de Santé (HAS) guidelines [9], a collective perspective will be adopted. The following costs will be included: blood transfusions, initial hospital stay, transportation and management of complications (primary endpoint). Costs will be collected prospectively over the 1-month follow-up period. Survival and quality of life data collected alongside the clinical trial will be used for Quality-adjusted Life Year (QALY) computation with the validated French value set [10].

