#### Blinding

Given the nature of the interventions, physicians, nurses, and patients cannot be blinded for the randomized intervention. A blinded adjudication committee will be conducted to confirm each endpoint.

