### Study outcomes

#### Primary endpoint

The primary endpoint measure is the percentage of patients without complication at the end of hospitalization in both arms. Complications are defined as: stroke, transient ischemic attack, acute coronary syndrome or elevated troponin, heart failure, arrhythmias or heart conduction disorder, deep vein thrombosis, pulmonary embolism, transfer to intensive care unit, death from any cause, new or progressive radiographic infiltrates, and transfusion-related infections.

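### Elevated troponin counts towards the primary endpoint but is scheduled only at inclusion, and the text and Table 1 disagree on whether any ECG follows inclusion

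*Protocol article*

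**What the plan says.** **Endpoint.** Under Primary endpoint: "The primary endpoint measure is the percentage of patients without complication at the end of hospitalization in both arms". The listed complications include "acute coronary syndrome or elevated troponin, heart failure, arrhythmias or heart conduction disorder". The abstract also lists a raised troponin level as an item of its own.

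**Troponin.** Data collection and follow-up states: "Creatinine level, blood count and troponin blood level will be collected at inclusion". In Table 1 the row "Laboratory tests – troponin" has one mark, at inclusion. The row for biological tests is separate. It is marked at inclusion, daily during the stay, at the end of hospitalization and at one month. The text defines the daily collection without troponin: "During the hospitalization stay, blood count and transfusion data will be collected every day until discharge".

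**ECG.** The same section says "an electrocardiogram will be performed at inclusion, the end of hospitalization stay and at 1 month after discharge". The ECG row of Table 1 is marked at inclusion only.

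**Blinding.** The trial is open label: "physicians, nurses, and patients cannot be blinded for the randomized intervention". The safeguard is this: "A blinded adjudication committee will be conducted to confirm each endpoint".

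**The concern.** A component defined by a laboratory value needs that value to be measured inside the endpoint window, in the same way in both arms. Here no troponin is planned after inclusion, so a patient can fail on this component only if someone orders the test. Those who order it know whether the patient receives one unit or two.

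The rhythm component is in the same position if sites work from Table 1. If they work from the text, one ECG falls inside the window. Sites reading different parts of the article could also assess the component differently.

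Two mechanisms matter in a non-inferiority comparison. If silent events are missed equally in both arms, a true difference is scaled down and non-inferiority is easier to declare. If one arm is tested more than the other, the difference moves towards or away from the margin, depending on which arm is watched more closely. With few expected events, a handful of test-driven ones carries weight.

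**Working it through.** **1. The plan's own figures.** Sample size calculation gives 93 % complication-free, a 10-point margin, 90 % power, alpha 5 % and 115 per arm. With unpooled variance and one-sided 5 %:

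n = (1.645 + 1.282)² × 2 × 0.93 × 0.07 / 0.10² = 111.5, so 112 per arm and 224 in total. This is within 3 % of the stated 230. One-sided 2.5 % gives 137 per arm (274), which does not reproduce it. That mismatch with the planned 95 % interval is a separate matter. Below I use the 95 % interval because it is the stated analysis.

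**2. Schedule against endpoint.**

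| Component | Text, after inclusion | Table 1, after inclusion | Scheduled in-window assessment |
|---|---|---|---|
| Elevated troponin | none | none | none on either reading |
| Arrhythmia or conduction disorder | ECG at end of stay and at 1 month | none | one ECG if the text governs, none if Table 1 governs |

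The 1-month ECG comes after discharge, outside the primary window. The text puts the questionnaires and the ECG on the same three visits. Table 1 keeps all three marks for the questionnaires and only one for ECG, so a mark lost in text extraction is an unlikely explanation.

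**3. Size of a small shift.** Expected failures per arm: 115 × 0.07 = 8.05. Three events in one arm: 3/115 = 2.6 points, about a quarter of the margin. The number three is my choice; the documents give no frequency for such events.

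Effect on the decision, with 8 failures in the two-unit arm and the upper 95 % bound of the difference in failure rates (unstratified), d + 1.96 × √[(p₁(1−p₁) + p₂(1−p₂))/115]:

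| Single-unit failures | Difference | Wald bound | Newcombe bound |
|---|---|---|---|
| 8 | 0.0 | 6.6 | 7.0 |
| 9 | 0.9 | 7.6 | 8.1 |
| 11 | 2.6 | 9.7 | 10.2 |
| 12 | 3.5 | 10.7 | 11.2 |

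Three more events reverse the conclusion from 9 to 12 with either interval. From 8 to 11 they reverse it only with the Newcombe interval.

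**4. Equal and unequal under-detection (my assumptions).** Let the true failure rates be 7 % and 17 %, exactly at the margin. Let a share f of failures be detectable only by a test, and let a proportion s of those be detected. The observed rate is the true rate × (1 − f + f·s).

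For f = 30 % and s = 50 % in both arms the factor is 0.85. The observed rates are 5.95 % and 14.45 %, the difference is 8.5 points, and the standard error is √[(0.0595 × 0.9405 + 0.1445 × 0.8555)/115] = 0.0395. The chance of falsely declaring non-inferiority is Φ((0.10 − 0.085)/0.0395 − 1.96) = 5.7 %, against a nominal 2.5 %.

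| f | s = 50 % in both arms | s = 50 % two-unit, 30 % single-unit |
|---|---|---|
| 20 % | 4.3 % | 6.2 % |
| 30 % | 5.7 % | 9.5 % |
| 50 % | 9.8 % | 21.5 % |

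**5. The opposite direction.** With no true difference (7 % in both arms), f = 30 %, and detection of 30 % in the two-unit arm and 50 % in the single-unit arm, the spurious excess in the single-unit arm is 0.07 × 0.30 × 0.20 = 0.42 points. So the sign depends on who is tested more. A 2.6-point shift at a 7 % failure rate would need f times the detection gap to equal 0.026/0.07 = 0.37, which is a demanding scenario.

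**The case against.** Several parts of the case against have force.

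- **ECG.** A reader might infer that both components rest entirely on clinicians choosing to test. For rhythm disorders that holds fully only if Table 1 governs. If the text governs, both arms have an ECG inside the window, and only transient in-stay events depend on clinically ordered recordings. This part of the objection stands. It leaves the troponin gap untouched.
- **Baseline values.** A reader might infer that an elevated inclusion value could itself count as failure. The documents do not support that: the abstract places complications during hospital stays, and an inclusion value reads naturally as a reference. What remains is that the article states no rule relating later values to it.
- **Committee.** A reader might infer that the committee sees only reported events. The article does not say how cases reach it, and such procedures may sit in documents not shown. The narrower statement holds: confirming endpoints does not by itself reveal a rise or rhythm change that nobody measured.
- **Severity wording.** The abstract restricts the endpoint to grade 3 or higher, and its list omits arrhythmia and conduction disorder. Whether a silent, test-only finding would qualify is therefore not certain. This tempers the size of the harm and is a further inconsistency to settle.
- **Recognised design.** Clinically triggered ascertainment with blinded adjudication is an accepted open-label approach. That lowers the severity. It does not resolve an explicit schedule that conflicts with itself on ECG and has no in-window measurement for a laboratory-defined component. For the same reason, condensation into an article does not excuse it.

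**Conclusion.** The point holds in this form. Elevated troponin is a primary component with no scheduled measurement in the endpoint window, on any reading of the article. Arrhythmia or conduction disorder shares that defect if Table 1 governs. Blinded adjudication addresses misclassification, not missed detection.

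The size is not known. The 2.6-point shift from three events is arithmetic on an assumed count. The false non-inferiority rates of 4.3 % to 9.8 % (equal detection) and 6.2 % to 21.5 % (less testing in the single-unit arm) rest on assumed shares and detection rates. A reader might infer that the plan favours the single-unit arm; the documents do not fix the direction. Equal under-detection favours non-inferiority, and unequal testing can go either way. This is a should-fix matter.

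**What to change.** 1. Reconcile the ECG row of Table 1 with the text so that an end-of-hospitalization ECG is recorded in both arms. The 1-month ECG may stay in the schedule, but it lies outside the primary window.
2. Run troponin on the end-of-hospitalization blood draw that Table 1 already schedules, in both arms, and judge it against the inclusion value.
3. Pass the inclusion and end-of-hospitalization ECGs and troponins of all patients, masked to arm, to the adjudication committee.

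**Cost.** One extra assay per patient on an existing draw, a table correction and more committee reading. A single discharge value will still miss rises that resolve during the stay, so the fix reduces the problem without removing it. It has to be in place before enrolment, because values not measured in the window cannot be recovered later.

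An alternative is to drop stand-alone troponin and count it only within an adjudicated acute coronary syndrome. That is a trade-off: it changes the primary composite, may unsettle the 93 % assumption, and still leaves the test to clinicians who know the arm.

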#### Secondary endpoints

Secondary endpoints are the of number of PRBC transfused up to 1 month after discharge, cost-effectiveness analysis; the number of patients with grade 3 or 4 bleeding, the number of patients with each complication defined in the primary endpoint, the number of transfusion- related events, number of days with hemoglobin level > 8 g/dL quality of life, duration of neutropenia, the time from randomization to last transfusion, the difference between the hemoglobin level immediately before and the day after transfusion, and the number of transfusion events without respect of the randomization arm. Transfusion-related events are defined as any complication declared by the physician to be related to the transfusion (fever, infection, pulmonary edema, etc.). Quality of life will be assessed using the FACT and QLC30 questionnaires. Neutropenia duration is the time spent with an absolute neutrophil count < 0.5 10^9^/L.

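### The cost list has no place for readmissions or day-hospital care outside the primary-endpoint complications, although costs, the assigned strategy and QALYs all run to one month after discharge

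*Protocol article*

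**What the plan says.** Cost is part of the trial's aim. The Objective section sets out to show that the single-unit strategy is "non-inferior to a two-unit transfusion in terms of severe complications and also leads to a cost reduction". The cost-effectiveness analysis is a secondary endpoint.

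Its scope is given in Data collection and follow-up. The perspective is broad: "a collective perspective will be adopted". Four items are then named: "The following costs will be included: blood transfusions, initial hospital stay, transportation and management of complications (primary endpoint"). The period follows at once: "Costs will be collected prospectively over the 1-month follow-up period".

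The complication item points to the primary endpoint, which is read at discharge: "The primary endpoint measure is the percentage of patients without complication at the end of hospitalization in both arms". The randomized strategy goes on longer. Under Treatment and study intervention, a patient in the experimental arm "will receive a single PRBC unit if their hemoglobin is below 8 g/dL during hospitalization and until 1 month after discharge", and the control arm has the same period. Units are counted over that period too: "number of PRBC transfused up to 1 month after discharge". EQ-5D and vital status, which feed the QALYs, are also taken at the one-month visit.

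**The concern.** The period over which costs are collected and the items to be costed do not match. The period extends a month past discharge, but the only hospital item is the first stay and the only complications are those of the primary endpoint. The Secondary endpoints section treats other events as outcomes in their own right, among them "the number of patients with grade 3 or 4 bleeding" and transfusion-related events such as fever. These are not listed as costs.

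A patient readmitted for such an event may lose quality of life or die, and this enters the QALYs. The hospital stay itself enters no cost item. If this care differs between arms, the incremental cost is wrong, and so is any ratio built on it. At stake is the cost conclusion. The primary non-inferiority conclusion is untouched.

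**Working it through.** The plan gives no figure to reproduce here. The check sets the stated windows and items side by side and then shows how a break-even depends on assumed costs.

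**Step 1: windows as stated in the Protocol article**

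| Element | Section | Runs to |
|---|---|---|
| Assigned strategy | Treatment and study intervention | 1 month after discharge |
| PRBC units counted | Secondary endpoints | 1 month after discharge |
| EQ-5D, vital status | Data collection and follow-up, Table 1 | 1-month visit |
| Cost collection | Data collection and follow-up | 1-month follow-up |
| Hospital cost item | Data collection and follow-up | end of the initial stay |
| Complication cost item | Data collection and follow-up, with Primary endpoint | unclear: discharge or 1 month |

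**Step 2: which post-discharge care has a place in the list**

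- Transfused units: yes.
- Transportation: yes, since it falls under the same one-month sentence.
- Complications of the primary-endpoint types: possibly. The parenthesis may name the type of complication or may import its cut-off at discharge.
- Readmission for grade 3-4 bleeding, fever or symptomatic anemia: no, except for the units and transport, unless the event also meets a primary-endpoint component such as intensive care transfer.
- Day-hospital visits: not named. They are covered only if the transfusion item is meant to include the visit as well as the blood.

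The data listed for the one-month visit are vital status, units given after discharge, length of stay and complications. Readmission is not among them.

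**Step 3: could such care differ by arm?**

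The Discussion itself raises the longer time at lower hemoglobin under single units. It also cites a retrospective study with 25 % fewer units. Suppose control patients receive N units, always in pairs, and that the 25 % applies:

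- control episodes = N / 2 = 0.5N
- single-unit episodes = 0.75N / 1 = 0.75N
- ratio = 0.75N / 0.5N = 1.5

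If that ratio held after discharge (an assumption), the experimental arm would make half as many visits again. Against this, fewer units could mean fewer transfusion-related events, and leaving those out would work the other way. The documents do not settle the net direction.

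**Step 4: break-even under assumed costs**

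Excess readmission rate that cancels the apparent saving = saving per patient / cost per uncounted readmission. Every amount below is an assumption, in arbitrary currency units.

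| Saving per patient | Readmission 3000 | 6000 | 10000 |
|---|---|---|---|
| 200 | 6.7 points | 3.3 | 2.0 |
| 500 | 16.7 | 8.3 | 5.0 |
| 1000 | 33.3 | 16.7 | 10.0 |

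The same sum can be done in blood units. Assume 8 units per control patient, so 0.25 × 8 = 2 are saved. If a readmission costs as much as 20 to 50 units, the break-even is 2/20 = 10 to 2/50 = 4 percentage points.

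The break-even ranges from a modest difference to an implausibly large one. The table shows only how the answer depends on inputs that the documents do not give.

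**The case against.** The strongest reply is that the article states its window. Costs are collected over one month, and the parenthesis most naturally names a kind of complication. Inpatient complication care already falls within the initial stay, so a separate complication item makes most sense if it reaches past discharge. Table 1 marks complications and adverse events in the one-month column. Bleeding or fever during the first stay is costed through that stay, and several transfusion-related events, infections for example, belong to the primary endpoint. The list is not called exhaustive, and an article leaves resource-use detail to the full protocol.

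Much of this stands. A reader might infer that all cost arising after discharge is lost. The documents do not support that: post-discharge units and transport are covered, and complications of the listed types may be. A reader might also set the break-even rates against the 10 % non-inferiority margin. That comparison is invalid, because the margin concerns primary-endpoint complications, which the list does cost, and says nothing about readmissions for other reasons.

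Two things do not yield. The hospital item is expressly the initial stay, and the complication item is expressly confined to the primary endpoint. These are stated limits on scope, so this is not a matter of omitted detail. Even on the most generous reading of the parenthesis, a readmission for bleeding, fever or symptomatic anemia contributes no stay cost.

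**Conclusion.** The point holds in a narrow form. Followed as written, the cost list leaves out readmissions and possibly day-hospital care in the month after discharge when the reason lies outside the primary-endpoint complications. It is also unclear whether complications of the listed types are costed after discharge. Two analysts could cost different events from the same sentence.

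Bias in the cost comparison needs a between-arm difference in the uncounted care. The documents give no unit costs, readmission rates or expected difference, and both arms keep the same 8 g/dL threshold after discharge. Size and direction are therefore unknown. It would be tempting to conclude that the planned cost reduction is false, or that the omission favours the single-unit arm. Neither is shown. The break-even range of 2.0 to 33.3 percentage points rests wholly on assumed costs.

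The matter concerns a secondary analysis, but one that serves half of the stated aim. It is worth a cheap correction.

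**What to change.** In the cost-effectiveness paragraph of Data collection and follow-up:

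- Replace the initial-stay item with all hospital stays and day-hospital visits from randomization to the one-month visit, readmissions included.
- State that complications are costed up to that visit, and include grade 3-4 bleeding and transfusion-related events with the primary-endpoint types.
- State that costs and QALYs use this same window.

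If this is not done, restrict the cost conclusion to the listed items and say so when reporting it.

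The change costs amended wording and a little more data entry, for readmissions and day visits, at a visit that already takes place. The cost estimate will also be noisier, since readmissions are likely to be few and expensive.
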